#### Disabilities of the arm

Evaluated through the Disabilities of the Arm, Shoulder and Hand (DASH) scale developed by Hudak et al. [45] and translated and validated for Brazil by Orfale et al. [46]. This instrument was developed to assess the disability and symptoms of single or multiple upper limb disorders. It contains 30 questions involving activities of daily living; symptoms of pain, tingling, and stiffness; and questions about social factors, work, sleep, and self-confidence. It has been used in other studies on patients with breast cancer [19].

#### Range of motion

To verify the ROM, evaluations of flexion, abduction, and external rotation of the shoulder according to previous studies with patients with breast cancer will be carried out [47] using a digital goniometer (Baseline Absolute Axis 360 degrees; Fabrication Enterprises, White Plains, NY, USA). The protocol used by Marques [48] will be performed for ROM assessment. The shoulder flexion movement will be performed with the subject lying down, and the flexion movement will be performed with the palm facing medially parallel to the sagittal plane. The fixed arm of the goniometer will be placed along the axillary line of the trunk, and the movable arm will be placed on the lateral surface of the humerus body facing the lateral epicondyle. For abduction, the individual must be seated. When performing the abduction movement, the palm of the hand will face anteriorly parallel to the frontal plane; the fixed arm of the goniometer should lie on the axillary line and posterior to the trunk; and the movable arm should lie on the posterior surface of the arm of the individual. In order to perform the external rotation, the position of the individual and the goniometer are the same; the individual will lie in the dorsal position, and the shoulder will be in abduction of 90 degrees, with the elbow flexed at 90 degrees and the forearm in supination. The arm of the goniometer should lie in the olecranon and the movable arm over the posterior region of the forearm directed to the third finger of the hand.

#### Strength of the upper limb

The muscle strength of the upper limb in both arms will be measured by the Chatillon® portable digital dynamometer (Ametek, Horsham, PA, USA), which can measure overall appendicular muscle strength and all body segments [49]. This equipment provides the value of the peak isometric maximum force exerted by the evaluated segment, and for this it requires a generation of fast force that does not fatigue the muscle. The maximum force generated is registered in newtons. The muscle groups responsible for flexion, extension, abduction, adduction, and internal and external rotation of the shoulder will be evaluated. The dynamometer will be placed over the specific location, and patients will be asked to perform force against the equipment for up to 5 s. Each muscle group will be evaluated three times, and the mean value of these evaluations will be used [50], with a 30-s interval between the tests, and bilaterally. In all cases, the patients will be instructed before the start and during the repetitions on the specific position.

#### Flexibility

The “sit and reach” test allows assessment of the flexibility of the coxofemoral joint [51]. The sit and reach box should be supported on a wall, and for evaluation, the patient is asked to keep the knees extended, bare feet resting in the sit and reach box, and hands overlapped on the horizontal surface of the box. The exercise should be performed with an anterior flexion of the spine, keeping the head between the arms, without flexing the knees, revealing a pause in the moment it reaches the maximum of the dotted line. Three replicates are performed, and the best mark among the three is considered.

#### Physical activity

The physical activity level will be investigated through the International Physical Activity Questionnaire (IPAQ–short version) [52]. The Brazilian validation and reproducibility were performed by Matsudo et al. [53] and had significant Spearman correlation and high reproducibility (rho = 0.69–0.71; *P* < 0.01) and validity of 0.75 observed compared with the instrument Computer Science & Applications (CSA; ActiGraph, Pensacola, FL, USA). It consists of six items that seek to verify the number of times the subject has practiced at least 10 continuous minutes of walking, moderate and vigorous physical activity, in the last week, in diverse involvements, namely labor, domestic, leisure, recreational, and sports. After completing the questionnaire, the participants can be classified into categories of sedentary, insufficiently active, and very active. The IPAQ also addresses the sitting time of individuals on weekdays and on weekends. There are two specific questions that ask: (1) How much time in total do you spend sitting on a weekday? and (2) How much time in total do you spend seated during on a weekend day? Data are presented in minutes per week.

#### Depressive symptoms

Depressive symptoms are investigated using the Beck Depression Inventory (BDI), a self-report questionnaire originally developed by Beck et al. [54]. It was validated in Brazil [55] and factorially validated for patients with cancer, indicating a Cronbach’s α of 0.82 [56]. It contains 21 multiple-choice objective questions related to depressive symptoms: sadness, pessimism, feeling of failure, dissatisfaction, guilty feelings, punishment feelings, self-dislike, self-criticism, suicidal thoughts, crying, irritability, and withdrawal from family or friends [56]. Each question provides four response options ranging from 0 to 3. The sum of the scores of each question provides a total score, ranging from 0 to 63, and the closer to 63, the greater the presence of depressive symptoms, indicating a higher degree of depression, and the greater the proximity to 0, greater the absence of depressive symptoms.

#### Pain

A visual analogue scale (VAS) will be used to assess pain. A VAS is a one-dimensional measure for assessing pain intensity. Composed of a 10-cm line with anchors at both ends, at one end of the line is marked “no pain” and at the other “worst pain imaginable.” The magnitude of the pain is indicated by marking the line, and a ruler is used to quantify the measurement on a scale of 0–100 mm [57].

#### Fatigue

Fatigue will be investigated by using the Functional Assessment of Cancer Therapy–Fatigue instrument (FACT-F). Validated in Brazil [58], it shows internal consistency of 0.91 for fatigue and 0.92 for the total FACT-F and has a total Cronbach’s α of 0.92. It is a self-report instrument aimed at patients with cancer that includes 13 items related to the perception of fatigue. Individuals will be asked to respond to each item with a score of 0 to 4, where 0 = not at all, 1 = a little bit, 2 = somewhat, 3 = quite a bit, and 4 = very much. In the total score, the possible interval is between 0 and 52, with a higher score indicating a level of less perceived fatigue.

#### Body image

Addressed by the Body Image After Breast Cancer (BIBCQ) questionnaire originally developed in Canada [59], which was translated, validated, and culturally adapted in Brazil [60] with values of Cronbach’s α for detailed internal validity for each scale, namely vulnerability (0.77), body stigma (0.86), concerns about the body (0.83), transparency (0.80), concerns about the arm (0.67), and limitations (0.72). This instrument aims to evaluate the body image after the diagnosis of breast cancer and can provide information related to the perceptions and attitudes regarding the side effects of breast cancer in the life of these patients. The BIBCQ is a questionnaire considered self-applicable, in which each item can be answered using a Likert scale. It consists of 44 questions divided into 6 scales, namely vulnerability, body stigma, limitations, concerns about the body, transparency, and concerns about the arm. In the end, the higher the score reaches, more compromised is the patient’s body image.

#### Self-esteem

The Self-Esteem Scale (EAR) developed by Rosenberg [61] will be used. This scale was validated for the population with cancer [62] and in Brazil [63]. It also received a validation review [64] with Cronbach’s α of 0.90. It is a one-dimensional measure consisting of ten statements related to a set of feelings of self-esteem and self-acceptance that determine global self-esteem. The total scale score varies from 10 to 40 points, and the following are used for categorization: (1) satisfactory or high self-esteem, those with a score greater than 31 points; (2) mean self-esteem, total score between 21 and 30 points; and (3) unsatisfactory or low self-esteem, scores less than 20 points. It is understood in this way that the greater the value reached by the woman on the scale, the better her self-esteem.

#### Sexual function

Sexual function is evaluated by the Female Sexual Function Index (FSFI) with cross-cultural validation [65], revealing a Cronbach’s α of 0.96. It is also validated internationally for patients with breast cancer [66] with Cronbach’s α of 0.70. This questionnaire consists of 19 questions grouped into 6 areas: desire, excitement, lubrication, orgasm, satisfaction, and pain. The sexual function score at the end of the analysis can vary from 2 to 36 points, considering that the higher the score obtained, the better the sexual function of the woman.

#### Sleep quality

Sleep quality is evaluated by the Pittsburgh Sleep Quality Index, which is validated [67] with a Cronbach’s α of 0.76. This instrument is composed of seven sleep-related areas: subjective quality, latency, duration, habitual efficiency, disturbances, use of sleeping medication, and daytime sleepiness. Scores range from 0 to 21 and correspond to overall sleep quality. In the end, scores up to 5 determine a good sleep quality and scores greater than 5 distinguish poor sleep quality.

#### Descriptive and control variables

The descriptive and control variables were divided into clinical variables (cancer stage, characteristics of treatment, previous clinical treatment, characteristics of surgical intervention, mammary reconstruction, date of surgery, presence of lymphedema, physiotherapy, and other diseases), sociodemographic variables (age, education, marital status, economic level, and occupation), and anthropometric measures (height and body mass). The descriptive and control variables will be acquired by self-report. The variables of the study regarding the Pilates solo and belly dance protocol are present in Table 3 and Fig. 2.

**Table 3 Tab3:** Study assessments

Outcomes	Instruments	Visits					
		Baseline	Postintervention	3-month	6-month	12-month	24-month
Primary							
Quality of life	European Organization for Research and Treatment of Cancer Quality of Life Questionnaire C30 (EORTC QLQ-C30) and Specific for Breast Cancer (EORTC QLQ-BR23)	√	√	√	√	√	√
Other outcomes							
Psychological							
Depressive symptoms	Beck Depression Inventory (BDI)	√	√	√	√	√	√
Pain	Visual analogue scale (VAS)	√	√	√	√	√	√
Fatigue	Functional Assessment of Cancer Therapy–Fatigue (FACT-F)	√	√	√	√	√	√
Body image	Body Image After Breast Cancer (BIBCQ)	√	√	√	√	√	√
Self-esteem	Rosenberg Self-Esteem Scale	√	√	√	√	√	√
Sexual function	Female Sexual Function Index (FSFI)	√	√	√	√	√	√
Sleep quality	Pittsburgh Sleep Quality Index	√	√	√	√	√	√
Physical							
Cardiorespiratory fitness	Cycle ergometer 6-min walk test	√	√	√		√	√
Lymphedema	Sum of the arm circumference	√	√	√	√	√	√
Physical activity	International Physical Activity Questionnaire (IPAQ–short version)	√	√	√	√	√	√
Disabilities of the arm	Disabilities of the Arm, Shoulder and Hand (DASH)	√	√	√	√	√	√
Range of motion	Goniometer test	√	√	√	√	√	√
Strength	Dynamometer test	√	√	√	√	√	√
Flexibility	Sit and Reach Test	√	√	√	√	√	√

**Fig. 2 Fig2:**
[figure not shown]
Template of recommended content for the schedule of enrollment, interventions, and assessments. *Source*: Standard Protocol Items: Recommendations for Interventional Trials (SPIRIT) 2013 statement: defining standard protocol items to clinical trials

#### Data collection

Data will be collected using an interview format with a paper questionnaire and physical tests. The principal investigator of the study, who received previous training, will conduct a 50-min interview. The questionnaire will cover general and clinical information, quality of life, and psychological variables. The physical variables will be investigated by the specific tests. All data collection will be administered before the beginning of the intervention (baseline collection) and after the conclusion of the 16-week protocol (postintervention collection), as well as 6, 12, and 24 months after intervention (maintenance collection) (see Fig. 1). The maintenance collection will take place considering the health behavior change that the belly dance and Pilates solo intervention can promote in women with breast cancer.

For the control group, data collection will be conducted using the same paper-based questionnaire and tests applied to the intervention group, with data on general and clinical information, quality of life, and physical and psychological variables. The collection will be scheduled with the participants and will take place at the same intervals as for the experimental group, before the start of the intervention (baseline collection) and after conclusion (postintervention collection) by the same principal investigator, as well as 6, 12, and 24 months after the intervention (maintenance collection). All the data collection of intervention and control groups will occur at Santa Catarina State University.

Patients who discontinue in the intervention or control group who did not show for the meeting will be collected as well and analyzed as an intention-to-treat group. During the intervention and data collection, the researchers will collect spontaneous feedback from the patients to guarantee that the study will not have any adverse events. Data from all groups (experimental and control) will be held according to the principles of good clinical practice and the Declaration of Helsinki and will be treated with confidentiality, following the current privacy policy.

#### Statistical analysis

First, a spreadsheet will be created using the Excel 2016 software (Microsoft, Redmond, WA, USA), from which the data will be transferred to IBM SPSS Statistics version 20.0 software (IBM, Armonk, NY, USA) for analysis. Descriptive statistics (mean, standard deviation, and percentage) for the characteristics of the sample will be computed. To investigate the relationship between general and health information of the control and experimental groups, chi-square or Fisher’s exact tests will be used. To analyze differences in the experimental and control groups in the baseline, postintervention, and maintenance periods, two-way analysis of variance with repeated measures and Holm-Šídák comparison tests will be conducted. Confounder variables will be considered in the analyses as type of treatment, type of surgery, age, and weight status. The analysis will be performed according to the protocol and intention to treat, meaning that all the patients will be evaluated according to the randomization process. Missing data will be handled using the multiple imputation method. The significance level of 5% will be two-sided.

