### Sample size

To calculate the sample size, the method of distinguishing between the means was used, being n = (α + β) 2 σ2/d2. The values of α = 0.05 and β = 0.80 were adhered to, for which, according to the Gaussian curve table, values of 1.64 and 0.84, respectively, were used. The difference between the means was obtained through the pilot study, and a variable considered for the calculation was quality of life, in which an average of the difference between all the scales in the before and after periods was found. This value of the expected selection was 6.15 ± 9.4. The expected variance (σ2) was 89.49. At the end of the analysis, after inclusion of a 30% margin of sample loss, a sample of 19 patients was selected for each group. Figure 1 shows the flow diagram of the study participants.

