### Pilates solo intervention

The women allocated to this group will participate in the Pilates solo protocol. The 16-week protocol will be implemented in 60-min Pilates solo classes three afternoons per week under supervision of an exercise science professional and a physiotherapist. The Pilates protocol will be divided into three stages:
*Warmup and stretching*: Including breathing, imprint and release, hip release, spinal rotation, cat stretch, hip rolls, scapula isolation, arm circles, head nods, and elevation and depression of scapulae exercises during warmup in all sessions.*Main stage*: A brief explanation of the purpose of the class will be provided, and the exercises will take place as detailed in Table 1. To increase the load during the protocol, TheraBand and toning ball exercises will be added at the 10th session; in the 20th session, the exercise in the arms will be added, and from the 24th session, the exercise of spinal rotation will be realized with weight of 1 kg. Exercises will be performed according to each patient’s ability (principle of sports training) to avoid pain (during and after exercising) and embarrassment associated with possible physical or even psychological and emotional difficulties.*Relaxation*: For this stage of the class, the patients will be invited to sit on the ball, spine stretch forward on the ball, self-stretch of cervical muscles on the ball (upper trapezius and scalene muscles), and actively mobilize the cervical spine. At the end of each class, a brief discussion will be held on the women’s perceptions regarding the objectives discussed in the beginning of class and whether they were achieved, and these data will be recorded by a third researcher to identify whether the participants enjoyed the class and felt that they achieved the objectives of the class.

**Table 1 Tab1:** Sixteen-week belly dance protocol (48 sessions) for women after breast cancer diagnosis (Florianopolis SC, Brazil, 2018)

	Session 1 Slow songs (up to 80 bpm) Medium songs (up to 120 bpm) Fast songs (up to 150 bpm)	Session 2 Slow songs (up to 80 bpm) Medium songs (up to 120 bpm) Fast songs (up to 150 bpm)	Session 3 Slow songs (up to 80 bpm) Medium songs (up to 120 bpm) Fast songs (up to 150 bpm)
1	Belly dance presentation	Belly dance presentation	Belly dance presentation
2	Loosening of hips	Loosening of hips	Pendulum and side hit
3	Pendulum and side hit	Movements and steps sequence	Pendulum and side hit with displacement

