### Belly dance intervention

Women allocated to this group will participate in the belly dance protocol. The 16-week protocol will be implemented in 60-min belly dance classes three afternoons per week under supervision of an exercise science professional and a physiotherapist. The classes will be divided into three stages:
*Warmup and stretching*: The beginning of the class will include songs with up to 80 beats per minute (bpm), thus identified as slow pace. The sequence of movements for this class stage will cover large movements involving specific joints, including flexion, extension, abduction, adduction, and rotation, initiated by the upper body until it reaches the lower limbs, lasting 10 min.*Main stage*: A brief explanation of the purpose of the class will be provided (i.e., the theory of dance or the specific step to be developed), followed by the practical part of the technical learning. The aim of this part will be for participants to learn the movements of the belly dance technique; to stimulate motor coordination, rhythm, and body awareness; and to improve aspects of flexibility and ROM of the upper limbs. The practice of the movements will be explored using individual, pair, or group dynamics involving movements corresponding to the rhythm of music or the rhythm stipulated for the women. The participants will have the artistic freedom to create their own pattern of movement based on the belly dance technique while respecting their own body awareness and allowing the expression of feelings. The evolution of the belly dance technique will be applied as outlined in Table 2. For this part of the classes, medium-paced music with up to 120 bpm will be used, as well as fast-paced music with up to 150 bpm. This part of the class will have an average duration of 40 min.*Relaxation*: This stage will be developed from slow-moving practices with music up to 80 bpm, usually the same songs used in the initial warmup and stretching. With heart rate normalization, this part will last 10 min. At the end of each class, a brief discussion will be held on the women’s perceptions regarding the objectives discussed in the beginning of class and whether they were achieved, and these data will be recorded by a third researcher to identify whether the participants enjoyed the class and felt that they achieved the objectives of the class.

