In a systematic review of dance and breast cancer published by our group, we identified dance as a viable alternative of adjuvant treatment for patients who have passed through breast cancer, as well as claiming that it can promote psychological benefits and improve strength and ROM of the upper limbs [72]. In this scenario, studies involving dance and breast cancer may involve specific dance therapy methods [15, 17, 28–30, 33]; traditional dance techniques, such as classical ballet and jazz [31]; the practice of traditional Greek dance associated with the training of the upper limbs [22]; as well as circular dance [32] and ballroom dance [33]. However, none of these studies presented published protocols demonstrating the importance of a belly dance protocol for women after the diagnosis of breast cancer. Further publication of a belly dance protocol will improve the possibility of generalization of the study, assuring the external validity.

The use of the Pilates method in patients with breast cancer was evaluated by a systematic review of four studies, and it was determined that the method leads to an improvement in patients’ ROM, pain, and fatigue [73]. Other evidence related to the benefits of the Pilates method for the health of these women supported improved quality of life, reduced pain and fatigue, decreased lymphedema, and increased upper limb functionality [21, 27, 37, 74]. These studies were published on Pilates interventions, but there is no protocol study for women with breast cancer. Also, the further publication of a Pilates solo protocol will improve the possibility of generalization of the study, assuring the external validity.

Methods of dance therapy are generally similar, taking advantage of subjective approaches to the perceptions of body and movement fluency in relation to feelings [15, 17, 28–30, 33]. These methods can comprise the use of conscious walks and drives, verbal feedback, exploration of specific body parts, the use of different movement intensities (light and slow to energetic and active), and the work in pairs [28]. These studies have shown positive results in relation to psychological and physical aspects of women after the diagnosis of breast cancer. However, they do not include the validation of a protocol, which, therefore, does not allow the study to be replicated by other researchers and does not indicate the frequency, duration, or intensity of the movements, as well as the beats per minute of the music used.

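### Both exercise arms are taught in shared classes but the stated ANOVA has no class term: if outcomes correlate within a class, the two-sided 5% is not kept, and with one class per arm class cannot be told from modality

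*Protocol article*

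**What the plan says.** Randomization and blinding process: individual patients are allocated to belly dance, Pilates solo or control.

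Pilates solo intervention and Belly dance intervention: both arms receive 60-minute classes for 16 weeks (48 sessions), held "three afternoons per week under supervision of an exercise science professional and a physiotherapist". The staffing wording is the same for both arms. Each class in both arms ends with a short discussion of how the women perceived it. For belly dance only, the article adds: "The practice of the movements will be explored using individual, pair, or group dynamics".

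Control group: three group meetings are held during the 16 weeks, partly so that these women form social ties.

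Statistical analysis: "two-way analysis of variance with repeated measures and Holm-Šídák comparison tests will be conducted". Type of treatment, type of surgery, age and weight status are to be considered as confounders. Neither class nor instructor is mentioned. On the error rate: "The significance level of 5% will be two-sided".

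Sample size: the formula for a difference in means is used with a 30% margin for loss, giving 19 per group. It contains no allowance for clustering.

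Background: the second hypothesis sets the modalities against each other, expecting Pilates to do better on physical variables and belly dance on psychological ones.

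**The concern.** Women who share a class three times a week for 16 weeks share its teaching, pace and company. The article's own rationale expects the social side to contribute: it lists social involvement as a feature of both activities, and its Discussion credits the social setting of dance. Outcomes of classmates, self-reported quality of life above all, may therefore be positively correlated after the intervention.

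A repeated-measures ANOVA accounts for correlation between visits of the same woman but not between women in the same class. Two things are then at stake.

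- **Error rate.** Any positive within-class correlation makes the standard errors of the exercise-arm means too small, so tests reject more often than the stated 5%. Holm-Šídák adjusts for the number of comparisons. It does not repair p-values that are too small to begin with.
- **Interpretation.** If an arm is one class, whatever is peculiar to that class is part of that arm's mean. A Pilates versus dance difference could then reflect two particular classes and not two modalities. If different staff teach the two arms, the instructor is entangled in the same way.

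**Working it through.** **Step 1. The plan's own figure.** Inputs from Sample size: "values of 1.64 and 0.84, respectively, were used", and "This value of the expected selection was 6.15 ± 9.4", with variance 89.49.

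n = (1.64 + 0.84)² × 89.49 / 6.15² = 6.1504 × 89.49 / 37.8225 = 14.55

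14.55 × 1.30 = 18.92, rounded up to 19.

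The stated 19 per group reproduces, and every term in it assumes independent women. (The 1.64 is a one-sided value although the analysis is two-sided. That is a separate matter and plays no part below.)

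**Step 2. Assumptions.** The documents do not give class size (m), number of classes or the within-class correlation (ICC). I assume:

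- one class of 19 per exercise arm or, alternatively, two classes of about 10;
- ICC of 0.01, 0.02, 0.05 or 0.10 on the outcome being compared;
- controls independent;
- equal arms and a normal approximation.

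**Step 3. Formulas.**

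- Design effect of an exercise-arm mean: DE = 1 + (m − 1) × ICC.
- True over model standard error, exercise versus control: k = √((DE + 1)/2).
- True over model standard error, Pilates versus dance: k = √DE.
- Actual error of a nominal two-sided 5% test: 2 × P(Z > 1.96/k).

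Example with m = 19 and ICC 0.05: DE = 1 + 18 × 0.05 = 1.90.

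- Exercise versus control: k = √1.45 = 1.204, 1.96/1.204 = 1.63, actual error 10.4%.
- Pilates versus dance: k = √1.90 = 1.378, 1.96/1.378 = 1.42, actual error 15.5%.

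**Step 4. Results.**

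| Class size | ICC | DE | k, exercise vs control | Actual error | k, Pilates vs dance | Actual error |
|---|---|---|---|---|---|---|
| 19 | 0.01 | 1.18 | 1.04 | 6.0% | 1.09 | 7.1% |
| 19 | 0.02 | 1.36 | 1.09 | 7.1% | 1.17 | 9.3% |
| 19 | 0.05 | 1.90 | 1.20 | 10.4% | 1.38 | 15.5% |
| 19 | 0.10 | 2.80 | 1.38 | 15.5% | 1.67 | 24.1% |
| 10 | 0.01 | 1.09 | 1.02 | 5.5% | 1.04 | 6.0% |
| 10 | 0.02 | 1.18 | 1.04 | 6.0% | 1.09 | 7.1% |
| 10 | 0.05 | 1.45 | 1.11 | 7.7% | 1.20 | 10.4% |
| 10 | 0.10 | 1.90 | 1.20 | 10.4% | 1.38 | 15.5% |

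Nineteen includes the loss margin, so fewer women may share a class to the end. With the full 30% lost, 19 × 0.70 is about 13. For m = 13 and ICC 0.01 to 0.10 the actual error is 5.7% to 12.1% against control and 6.4% to 18.6% for Pilates versus dance.

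**Step 5. Identifiability.** With one class per arm, the class indicator and the arm indicator are the same variable. No model can estimate a class effect from such data. The size of the problem can then only be shown over assumed correlations.

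**The case against.** The strongest reply is that the size of the problem rests on facts the article does not give. Class numbers and staffing are details an article may leave to the full protocol, and variance-model detail may sit in an analysis plan. I do not count their absence as a fault. What stands is that the article does fix a model for arms taught in classes, and that model has no term for the class.

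Several stronger readings are tempting but go beyond the documents:

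- **That the standard errors are certainly too small.** This needs a correlation above zero. At zero there is no inflation, and at 0.01 with classes of 10 the error is only 5.5% to 6.0%.
- **That instructor and modality are necessarily confounded.** The identical staffing wording leaves open that the same two professionals teach both arms. The instructor would then be common to Pilates and dance, and that contrast would be largely protected from an instructor effect. Class composition would still be tied to modality.
- **That both arms do pair and group work.** This is stated only for dance. For Pilates the group format follows from the word classes and the closing discussion.
- **That the model contains group and time only.** Patient-level confounders are named too. They do not stand in for class.
- **That the Discussion claims its results will generalise whoever teaches.** The sentence reads "Further publication of a belly dance protocol will improve the possibility of generalization of the study, assuring the external validity". It concerns publishing the protocol so that others can repeat it, and says nothing about class or instructor effects.

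Two further points are fair. Part of what a class shares is intended treatment, so for exercise versus control it is not simply a nuisance. The uncertainty from having very few classes remains all the same. Controls also meet as a group three times, so they are only approximately independent. Positive correlation among them would add to the inflation against control.

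**Conclusion.** The point holds conditionally. Both exercise arms are taught in shared classes, and the stated analysis and sample size treat women as independent. If outcomes correlate positively within a class, the stated two-sided 5% is too optimistic.

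With one class of 19 per arm and an assumed correlation of 0.01 to 0.10, the actual error is about 6% to 16% for exercise versus control and 7% to 24% for Pilates versus dance. With classes of 10 it is about 5.5% to 10% and 6% to 16%. The 24% is the upper corner of the assumed range and not an expected value.

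With 19 per arm, one or very few classes per modality is likely, although the article does not say so. With exactly one, class and modality cannot be separated, and neither can the instructor if staff differ between arms. The second hypothesis is the most exposed.

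**What to change.** 1. Record the class and the lead instructor for every session, starting now, because Trial status says enrolment is under way and this may not be recoverable later.
2. If an arm is run in several classes, add a random class effect for the exercise arms only (a partially nested model), with a small-sample correction to the degrees of freedom. Note that the three control meetings make the independence of controls approximate.
3. If there are only one or two classes per arm, keep the stated model. Beside its results, report confidence intervals and p-values with standard errors multiplied by √((DE + 1)/2) for exercise versus control and √DE for Pilates versus dance, at assumed within-class correlations of 0.01, 0.02, 0.05 and 0.10 and the actual class size.
4. In that case, word the conclusion, especially for Pilates versus dance, as the effect of the classes as delivered in this trial.

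The cost is a class and instructor entry on the attendance sheet, a clause in the analysis section and more restrained wording. No extra patients and no change of staff are needed. The downside is wider intervals (with one class of 19, by a factor of 1.04 to 1.38 against control and 1.09 to 1.67 between modalities over the assumed range) and a narrower claim.
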